### Intervention adherence

The use of the i-CBT platform will be assessed and recorded, including the number of modules that are completed, the usage of tools within the platform and the number of weekly reviews attended, whether asynchronous feedback or remote videoconferencing. A minimum intervention dose for the app will be defined a priori, with “compliance” defined as completion of a pre-specified minimum level of usage of the i-CBT (at least 4 modules completed of the core 8 modules in the treatment package).

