The intervention will be identical by content and design between the guided versus unguided versions, except for the provision of support and contact from a CBT-trained therapist (Psychological Wellbeing Practitioner) for the guided version. Psychological Wellbeing Practitioners (PWPs) are a UK-specific workforce specifically trained to be competent in supporting structured low-intensity interventions such as guided CBT following a standardized British Psychological Society (BPS)-accredited nationally commissioned APT training course (e.g. PGCert/GradCert Psychological Therapies Practice-Low Intensity Cognitive Behavioural Therapy), involving 45 days of academic work (one day per week) alongside supervised practice within a local NHS Talking Therapies service over 12 months. Such courses are typically completed by psychology graduates, who deliver low-intensity interventions for anxiety and depression in the Talking Therapies services of the NHS in England. These training courses directly evaluate competence in supporting guided CBT, and thus, any successful course graduate and practising PWP would be eligible to deliver this intervention.

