In the guided version, the PWP will welcome the participant to the platform upon signup and offer an initial optional call to discuss their specific difficulties and to tailor treatment; thereafter, the PWP will provide contingent feedback and support when users complete the next intervention module on the platform, with PWP and participant collaboratively agreeing on a timescale to complete the next module and for the next review session, typically after 1–2 weeks. This feedback can take the form of 15–30 min of videoconference or telephone calls or asynchronous written feedback within the treatment platform, tailored to the preference of the participant (i.e. a blended model for many students). Templates will be used for written feedback to ensure fidelity and adherence to the treatment model: for participants who receive a videoconference or telephone call, this will summarize the content of the call; if there is no call, it will review what the participant has done in the Internet platform and refocus them on the next module. The feedback will focus on supporting and encouraging participants, addressing their questions, providing guidance to revisit sections or practice particular exercises and giving access to relevant supplementary modules. The PWPs will monitor sign-up to the unguided platform and will send reminders to students who have not accessed the intervention.

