Secondary analysis will be undertaken including:Complier Average Causal Effect (CACE) analysis [68, 69] to provide an estimate of a treatment effect accounting for pre-specified per-protocol adherence and compliance with the treatment, whilst retaining the benefits of randomization.The extent of missing data will be considered, and where necessary, in agreement with the Trial Steering Committee (TSC), imputation (e.g. doubly robust estimation combining propensity score models with multiple imputation to reduce risk of bias) will be used to adjust for loss to follow-up.Exploratory mediation analyses will be undertaken to gain insight into mechanisms that could explain the potential effect of the interventions on primary outcomes. We will use modern causal inference methods using structural equation modelling or parametric regression models to assess mediation effects [70]. For mediation analyses of longitudinal data, assuming ICC = 0.5, the sample sizes to achieve MCID calculated above can detect small effect sizes for mediators (β = 0.14) in RCTs (with up to 8 micro-repeated assessments), at power = 0.80. A series of models will be performed for each outcome, investigating the mediation effect of each mediator variable individually and the mediation effect of each mediator variable in an overall model combining all mediators. The mediation effect will be reported as the indirect effect of treatment via the specified mediator, with a 95% confidence interval and the proportion of the total intervention effect mediated. Analyses will include the use of instrumental variables to account for effects of unobserved confounding on mediators [68].In addition, the ITR analysis will include composite baseline predictors estimated using nested cross-validation machine learning methods, to assign each participant a predicted probability of adherence to self-guided i-CBT and a separate predicted probability of adherence to guided i-CBT. The use of such composite measures as predictors in developing the ITR will make it possible to distinguish heterogeneity in treatment effects due to predicting differential adherence versus differential effectiveness of the two interventions given adherence.The results of all models will be compared to primary analysis complete case ITT results.

Analyses will be undertaken by a statistician blinded to group allocation and using Stata v.17 and R 4.5.0.

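### The compliance rule behind the CACE analysis counts modules, which students in both arms can complete, and not the practitioner guidance that randomization assigns

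*Protocol article*

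**What the plan says.** Under Intervention adherence, the protocol article sets compliance in advance as "at least 4 modules completed of the core 8 modules in the treatment package". The same section records how many reviews each participant attended, by call or written feedback, but these do not enter the definition.

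Under Guided and unguided i-CBT, the treatment is "identical by content and design between the guided versus unguided versions, except for the provision of support" and contact from a practitioner. Guidance starts early: "In the guided version, the PWP will welcome the participant to the platform upon signup and offer an initial optional call". Feedback then follows each completed module.

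Under Statistical analysis plan, a secondary CACE analysis is planned "to provide an estimate of a treatment effect accounting for pre-specified per-protocol adherence and compliance with the treatment, whilst retaining the benefits of randomization". The same list gives each participant a "predicted probability of adherence to self-guided i-CBT and a separate predicted probability of adherence to guided i-CBT", so that the treatment rule can separate "differential adherence versus differential effectiveness of the two interventions given adherence". The article does not state the CACE estimator, the instrument, or the arm or arms in which compliance is counted.

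**The concern.** A CACE analysis uses randomization to learn about an exposure that randomization changes directly. Here randomization changes guidance. The compliance variable is module use, which is open to both arms and is itself an outcome that guidance may raise. An unguided student can comply fully without any of the support under test. A guided student who has had the welcome contact, the optional call and feedback on three modules is a non-complier.

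With arm as instrument, the analysis attributes the whole difference between arms to passing four modules. That requires the exclusion restriction: guidance must change outcome only by moving students past the threshold. The protocol describes practitioners tailoring treatment, answering questions and directing practice, and it plans for the two versions to differ in effectiveness at equal adherence. If they do, the restriction fails. The risk is an adherence-adjusted figure that is too large and is read as the benefit of guidance to those who engage with it.

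**Working it through.** The article states no completion rate and no CACE figure, so there is nothing to reproduce. The check shows what the stated compliance variable implies.

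**Inputs.** The PHQ-9 difference of 2.59 and SD of 5.4 come from the Sample size section and serve only as illustration. The shares completing four or more modules, pG (guided) and pU (unguided), are assumptions. pG is held at 60% and pU runs from 10% to 50%.

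**Formulas.**
- Standard two-arm instrumental-variable CACE: ITT / (pG − pU), multiplier 1/(pG − pU).
- Comparator: ITT / pG, multiplier 1/pG. This is the guidance effect among students who complete under guidance, if guidance does nothing for the other guided students.
- Inflation of the first over the second: pG / (pG − pU).

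| pG / pU | 1/(pG − pU) | 1/pG | Inflation |
|---|---|---|---|
| 60 / 10 | 2.0 | 1.67 | 1.2 |
| 60 / 20 | 2.5 | 1.67 | 1.5 |
| 60 / 30 | 3.3 | 1.67 | 2.0 |
| 60 / 40 | 5.0 | 1.67 | 3.0 |
| 60 / 50 | 10.0 | 1.67 | 6.0 |

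As an example, take an ITT difference of 2.59 points and rates of 60/40. The module-based CACE is 2.59 / 0.20 = 12.95 points, or 12.95 / 5.4 = 2.4 SD. Division by pG gives 2.59 / 0.60 = 4.32 points.

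**Dependence on how guidance works.** The assumed true effect is −2 points in those whom guidance helps.

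1. Guidance helps everyone who completes four modules under guidance, and nobody else. ITT = 0.6 × (−2) = −1.2. The module-based CACE is −1.2/0.4 = −3.0 at 60/20 and −1.2/0.1 = −12.0 at 60/50. A simulation of 400,000 participants per scenario gave −2.99 and −12.13. Dividing by pG returns −2.0.
2. Guidance helps every guided student. ITT = −2. The module-based CACE is −2/0.4 = −5.0 at 60/20 and −2/0.1 = −20 at 60/50, which is 2.5 to 10 times the true effect. Dividing by pG also overshoots: −2/0.6 = −3.3.
3. Guidance helps only students it induces to complete. At 60/20, ITT = 0.4 × (−2) = −0.8 and the CACE is −0.8/0.4 = −2.0. That is correct for induced completers, but the average over all completers under guidance is −0.8/0.6 = −1.33. At 60/50 that average is −0.2/0.6 = −0.33.

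Only in the third case is the estimator valid, and there it answers a question about module completion in a subgroup.

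**The case against.** The strongest reply is that the two-arm estimator is assumed. The article names CACE and leaves the estimator open, as articles commonly do. If compliance were counted only in the guided arm, the multiplier would be 1/pG, or 1.4 to 2.5 for pG from 70% to 40%, and the largest inflations would disappear. This stands, and it limits any claim about size. It does not rescue the definition: guided students who had contact but completed fewer than four modules would still break the exclusion restriction, as the second case above shows.

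A reader might infer that the CACE will certainly be biased, or inflated several-fold. The documents support neither. If few unguided students complete, inflation is only about 1.2 to 1.5 times. If guidance works purely through completion, the estimate is right for induced completers, and the fault is an unnamed estimand.

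A reader might also infer that adherence is handled nowhere else. The treatment-rule analysis models adherence by arm, and all models are to be compared with the primary result. That limits misreading of an extreme CACE, but it does not supply a causal estimate of the effect of receiving guidance.

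Finally, counting reviews is not a clean cure. Feedback follows module completion, so a high contact threshold would bring back the same problem. Practitioners also send reminders to unguided students who have not logged on, so contact in that arm is not strictly zero.

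**Conclusion.** The point holds as a mismatch between a stated definition and the randomized contrast. It is not a complaint about missing detail: the article fixes the compliance variable and names the analysis that relies on it. A standard CACE on that variable would estimate the effect of passing four modules in students induced to do so, under an exclusion restriction at odds with the protocol's own premise.

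The size is conditional. Against division by guided completion, inflation is about 1.2 to 6 times for assumed rates of 60/10 to 60/50, and it reaches 3 times only when the gap between arms is at most one third of guided completion. These figures rest on assumed rates and an assumed estimator. Only a secondary analysis is affected; the primary ITT comparison, the sample size and the randomization are not. It should be fixed before unblinding.

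**What to change.** Define the CACE exposure as receipt of practitioner guidance, with a low threshold such as any review contact, by call or written feedback. Reviews are already recorded and are not offered in the unguided arm, so non-compliance becomes one-sided. State the exclusion assumption that remains (the welcome contact in guided students below the threshold, and the reminders to unguided students) and add a sensitivity analysis for it. Keep four or more core modules as a descriptive adherence measure or a mediator.

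If the module-based CACE is retained, state its estimator, label it as the effect of module completion among students induced to complete, and do not present it as the effect of guidance.

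The cost is one definition, a sentence on assumptions and a small amount of extra analysis. No new data are needed. A residual exclusion assumption remains for guided students below the threshold.

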### Outcomes

Outcomes will be assessed at baseline (pre-randomization) and 3 months post-randomization.

#### Primary outcome

The primary outcome measures will be the mean symptoms of anxiety (GAD-7) and depression (PHQ-9) at 3 months (primary endpoint) adjusted for baseline scores.

#### Secondary outcomes

Secondary outcomes include the mean scores at 3 months adjusted for baseline scores: the Warwick-Edinburgh Mental Wellbeing Scale (WEMWBS) [47], a widely used and well-validated measure of wellbeing; PSWQ-S [40] and RRS-B [41] to measure worry and rumination; and the Work and Social Adjustment Scale (WSAS) [48], a frequently used measure of functioning with respect to work/education, home management, social leisure, private leisure, and close relationships, each rated from 0 not at all impaired to 8 severely impaired. The Brief Resilience Scale [49] will assess students’ self-reported resilience. A bespoke questionnaire will assess the mean use of university-based and non-university-based healthcare (including National Health Service) services, resources, and support during the 3-month follow-up period. Another bespoke questionnaire will ask participants to report on the actual academic marks and their academic targets for the previous year and whether they were satisfied with their academic progress.

Participants will be asked to complete brief measures each week for 8 weeks after randomization to provide potential mediators of change: a two-item measure of depression (PHQ-2) [50]; a two-item measure of anxiety (GAD-2) [51]; a single-item measure of stress over the last week (scored 0 none to 4 very severe); six items from the Cognitive and Behavioural Response to Stress Scale [52] assessing the frequency and usefulness of use of cognitive reinterpretation, behavioural activation, and relaxation or meditation strategies; 3-item adaptations of the automaticity component of the Self-Report Habit Index [53] focused on assessing the extent to which worry and problem-solving respectively are each a habit (e.g. “something that I do automatically” “I do without thinking”) over the past 7 days; 2-items from the Self-Compassion Scale-short-form [54]; 2 items from the RRS-Brooding 5-item questionnaire [41]; a one-item measure assessing self-efficacy (“In the last seven days I feel better prepared to handle situations I could not handle before” rated using a seven-point Likert scale ranging from − 3 (“absolutely not true), 0 (“neither nor”) to + 3 (“absolutely true”) and a one-item measuring problem clarification (“In the last seven days, I understand myself and my problems better” rated using a seven-point Likert scale ranging from − 3 (“absolutely not true), 0 (“neither nor”) to + 3 (“absolutely true”).

The following descriptive variables will be assessed only at baseline: age, gender, sexuality, year of study, course of study, ethnic group, educational level. The extensive battery of potential prescriptive predictors to inform the development of an ITR will only be assessed at baseline.

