**Methods:**

An online single-blind, two-arm parallel-group randomized controlled trial to examine symptoms of depression and anxiety across 3 months in university students aged over 16 who screen into the study with self-reported high levels of anxiety (GAD-7 > 9) and/or depression (PHQ-9 > 9). Eligible participants will be randomized to guided transdiagnostic iCBT supported by a psychological wellbeing practitioner or to the same transdiagnostic iCBT content as unguided self-help. In total, 720 participants with no current bipolar disorder or psychosis will be recruited from UK universities. Assessments will take place at baseline (pre-randomization) and 3 months post-randomization. Primary endpoints and outcomes are self-reported depression and anxiety symptoms at 3-month follow-up, adjusting for baseline scores. Well-being, health-related quality of life, functioning and academic outcomes are secondary outcomes. Compliance, adverse events, and potentially mediating variables will be monitored. We will use machine learning to estimate heterogeneity of treatment effects and develop an ITR to optimize the allocation of students to either unguided or guided iCBT.

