### Baseline and follow-up assessments

The baseline assessment will take place after electronic informed consent to participate in the trial is provided and consists of web-based self-report measures to assess current and lifetime history of depression, current wellbeing, symptoms of anxiety and depression, social and work functioning, use of services and treatment received, academic grades, resilience, and stressful events (see outcome measures and Fig. 1—SPIRIT figure, Table 1). The Lifetime Depression Assessment Self-report questionnaire (LIDAS) [39] will be used to assess lifetime major depression (MDD) diagnosis according to DSM criteria and is largely based on the widely used Composite International Diagnostic Interview (CIDI). The LIDAS has been proven to be effective for determining history of depression through self-report in an online digital format, matching the needs for the current study [39]. The instrument consists of a conditional sequence of pre-programmed questions assessing all the diagnostic criteria for depression, with logic cut-outs so that subsequent questions are determined by prior questions, keeping the assessment brief.

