**Fig. 1 Fig1:**
[figure not shown]
Schedule of enrolment, interventions, and assessments (SPIRIT figure)

**Table 1 Tab1:** Measurements and endpoints

**Web Assessment**		**Baseline**	**Follow-up (3 months)**
Pre-screening	date of birth, self-reported mental health	YES	NO
Informed consent			
Socio-demographics	Age, sex, employment status, ethnicity, historic mental health problems	YES	NO
Depression	PHQ-9 questionnaire; primary outcome	YES	YES
Anxiety	GAD-7 questionnaire; primary outcome	YES	YES
LIDAS	Incidence of current and past major depressive episode	YES	NO
Rumination	RRS-Brooding questionnaire; secondary outcome	YES	YES
Worry	PSWQ questionnaire; secondary outcome	YES	YES
Wellbeing	WEMWBS questionnaire; secondary outcome	YES	YES
Resilience	BRS questionnaire; secondary outcome	YES	YES
Perceived stress	PSS-4 questionnaire; secondary outcome	YES	YES
Stressful events	ASQ questionnaire; secondary outcome	YES	YES
Use of mental health services and resources		NO	YES
Academic outcomes		YES	YES

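### Academic marks at the 3-month follow-up are asked for over the previous year, so most or all of the reported period pre-dates randomization and a null result on marks would be uninformative

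*Protocol article*

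**What the plan says.** The abstract lists academic results among the secondary outcomes: "Well-being, health-related quality of life, functioning and academic outcomes are secondary outcomes". The Outcomes section gives two assessment times only: "Outcomes will be assessed at baseline (pre-randomization) and 3 months post-randomization". Table 1 marks the row "Academic outcomes" as collected at both. The baseline battery, under Baseline and follow-up assessments, already includes "use of services and treatment received, academic grades, resilience, and stressful events".

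The content of the measure is given in one sentence under Secondary outcomes. A bespoke questionnaire asks students to "report on the actual academic marks and their academic targets for the previous year" and "whether they were satisfied with their academic progress". The marks and targets carry a one-year window; the satisfaction item carries none. The article does not say that the follow-up version differs from the baseline version.

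The sentence just before it, on the other bespoke questionnaire, limits service use to "services, resources, and support during the 3-month follow-up period". The Statistical analysis plan section compares continuous secondary outcomes between arms at 3 months, adjusted for baseline scores.

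**The concern.** A mark awarded before randomization cannot depend on the allocated arm. A one-year look-back taken 3 months after randomization mostly collects such marks, so the item is a sensible baseline covariate but a poor 3-month outcome. The neighbouring service-use item was aligned with the trial period; this one, as described, was not.

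The interpretation of a secondary result is at stake. The Discussion opens by linking anxiety and depression to lower grades and drop-out, so readers will look at the academic result. If the arms do not differ on marks, the result could be taken to mean that guidance does not help academic performance, when the item had little or no capacity to show it.

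**Working it through.** The plan states no power or effect size for this outcome, so there is no figure to reproduce. The check compares windows, then looks at what the planned adjustment does.

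**Inputs from the protocol article.** Recall window: one year. Follow-up: 3 months, with none later. Recruitment target: 720. Attrition: 20%, as assumed in the Sample size section. Analysed per arm: 720 × 0.80 / 2 = 288.

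**1. Rolling-year reading**
- Share of the window after randomization: 3/12 = 25%; before: 9/12 = 75%.
- Those 9 months also lie inside the baseline window, so the two answers overlap by 9 months.
- With marks spread evenly over the year (assumption), a difference Δ in post-randomization marks appears as 0.25 × Δ in the yearly average.

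**2. Academic-year reading** (assumption: teaching from October to June, 9 months, randomization at the start of a month)
- If students count the year as previous only from October: for randomization from October to June, both answers describe the same completed year. For July to September they describe different years, but the later one ended before randomization. Post-randomization share: 0% in all 12 months.
- If they count it as previous from the end of June: randomization in April, May or June gives 3/9 = 33%, 2/9 = 22% or 1/9 = 11%. The other 9 months give 0%.

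**3. Effect of baseline adjustment under the rolling reading**

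Illustrative model (assumptions): a year's mark is the mean of four equal quarters, each with SD 1 and pairwise correlation r. The true effect is 0.20 SD on the one post-randomization quarter. Tests are two-sided at 0.05 with 288 per arm, so the standard error of a standardized difference is √(2/288) = 0.0833.
- Effect on the yearly mean: 0.20 × 0.25 = 0.05 in quarter-SD units.
- Variance of the yearly mean: V = (1 + 3r)/4. Standardized effect: 0.05/√V, which is 0.10 at r = 0, 0.063 at r = 0.5 and 0.05 at r = 1. So 0.05 is the floor of the range.
- Covariance of the baseline and follow-up means (three shared quarters among 16 pairs): (3 + 13r)/16. At r = 0.5, V = 0.625, the covariance is 0.594 and the correlation is 0.594/0.625 = 0.95.
- Residual SD after adjustment: √[0.625 × (1 − 0.95²)] = 0.247. Adjusted standardized effect: 0.05/0.247 = 0.20.

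| Analysis at r = 0.5 | Power |
|---|---|
| Yearly mark, unadjusted | 0.12 |
| Yearly mark, baseline-adjusted, error-free reports | 0.68 |
| Same, reporting error 5% of the variance of each answer | 0.40 |
| Same, reporting error 20% | 0.18 |
| Marks since randomization, adjusted for previous-year mark, error-free | 0.87 |

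The last row uses residual variance 1 − 0.5²/0.625 = 0.60, so the effect is 0.20/√0.60 = 0.26. In every adjusted yearly-mark row the estimated raw difference is still 0.05, a quarter of the true 0.20. Under the academic-year reading with no post-randomization marks, the expected difference is zero with or without adjustment.

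**The case against.** The strongest reply is that one condensed sentence describes an instrument the reader cannot see. It covers both time points, and the follow-up form may be worded differently. Grammatically, the one-year phrase could also attach only to the academic targets, which would leave the marks with no stated window. This stands as a limit: the fault is shown in the published wording, not in the form. The article still states one window and no other.

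The share of marks also need not equal the share of calendar time. If assessments cluster in the 3 months after randomization, more than a quarter of the marks could be post-randomization. The article gives no assessment calendar, so this stands too, and for the same reason the 0% figure under the academic-year reading is conditional.

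Two stronger readings are tempting. A reader might infer that the academic comparison must come out null by construction. The text does not support that: under the rolling reading an effect is diluted, not abolished, and the satisfaction item has no stated window and may respond to treatment. A reader might also infer that adjusting for an overlapping baseline answer makes matters worse. Under the rolling reading it does the opposite, because it removes the variance of the shared months. Power computed for an unadjusted comparison would therefore understate what the planned analysis can do.

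Finally, marks are one of several secondary outcomes and appear in neither the objectives nor the hypotheses. That limits the consequence but does not make the item informative.

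**Conclusion.** The concern holds in a limited form. As written, 75% of the marks window by calendar time precedes randomization if the year is rolling. If the previous academic year is meant, usually all of it does: 100% under one assumed calendar, and 67% to 100% under the other. The between-arm difference in marks is then diluted about fourfold (rolling year, evenly spread marks), or can show little or nothing (academic year). Either way, a null result on marks would be uninformative.

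Baseline adjustment recovers part of the power under the rolling reading, and how much depends on how accurately students report. It does not undo the dilution, and it rescues nothing when the same completed year is reported twice.

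The conclusion rests on the published window applying at follow-up. The size of the dilution rests on even spread of marks, and the power figures on the illustrative model. The primary outcomes and the sample size are untouched.

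**What to change.** Limit the follow-up marks item to work assessed since randomization, in line with the service-use item, and keep previous-year marks as a baseline covariate or predictor.

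If the form can no longer be changed, report follow-up marks descriptively only and keep satisfaction with progress as the academic outcome. If the follow-up form already uses another window, correct the published wording.

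Each option is a one-line change to the questionnaire, the outcome list or the text. The Trial status section describes recruitment as ongoing, with data collection ending 4 months after it closes; if the form is changed part-way, marks collected under the two wordings should be kept apart. The cost of re-anchoring is that some students will have no mark in the window, so the number analysed for this outcome will be smaller.

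### Weekly PHQ-2 and GAD-2 are planned as mediators of their own parent scales (3-month PHQ-9 and GAD-7), so the matched-pair results say nothing about mechanism and a parallel combined model understates process measures that act through early symptoms

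*Protocol article*

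**What the plan says.** All references are to the protocol article.

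- **Primary outcome** defines the endpoints as "the mean symptoms of anxiety (GAD-7) and depression (PHQ-9) at 3 months (primary endpoint) adjusted for baseline scores".
- **Secondary outcomes** introduces the weekly battery as "brief measures each week for 8 weeks after randomization to provide potential mediators of change: a two-item measure of depression (PHQ-2"), followed by "a two-item measure of anxiety (GAD-2"). The same list holds single-item stress, items on coping strategies (reinterpretation, behavioural activation, relaxation), habit automaticity, self-compassion, brooding, self-efficacy and problem clarification. All have the same status.
- **Statistical analysis plan** gives the purpose of the exploratory mediation analyses: to "gain insight into mechanisms that could explain the potential effect of the interventions on primary outcomes". The models are then fixed: "A series of models will be performed for each outcome, investigating the mediation effect of each mediator variable individually", and also "the mediation effect of each mediator variable in an overall model combining all mediators". Each result is to be reported as an indirect effect with a 95% confidence interval and a proportion mediated.

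Nowhere are the two symptom scales set apart from the process measures, given another role, or left out of the model for their own outcome.

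**The concern.** PHQ-2 and GAD-2 are two-item measures of the same symptoms that PHQ-9 and GAD-7 measure at 3 months. A mediator is meant to be something different from the outcome that carries the effect to it. An early reading of the outcome does not meet that description. Finding that lower depression in weeks 1 to 8 goes with lower depression at 3 months shows that the effect began early and lasted. It does not say how the effect came about.

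There are two consequences. First, the matched single-mediator model will return a sizeable proportion mediated whenever the effect is early and durable, and that figure could be read as a mechanism. Second, early symptoms may lie downstream of the coping, habit and brooding measures. Entering them beside those measures blocks part of the route under study and moves credit from the process measure to the symptom scale.

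At stake is the reading of the mechanism results, in particular the combined-model proportions mediated.

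**Working it through.** The article gives no figure to reproduce here, so the check is a linear illustration. Its path values and reliabilities are **assumptions**; the article states neither.

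**Model.** Arm T shifts a mechanism M by a. The week-8 symptom is S = b·M + e. The 3-month outcome is Y = c·S + d·M + error. The brief scale P is S plus measurement error, with within-arm reliability r. M carries 100% of the treatment effect by construction. Let

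- f = cb/(cb + d), the share of M's effect that passes through week-8 symptoms;
- q = the within-arm proportion of the variance of S explained by M.

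**Values.** a = 0.4, b = -0.5, c = 0.7, residual variances of M and e equal to 1. Then q = 0.25/(0.25 + 1) = 0.20. Two cases are taken: f = 1 (d = 0) and f = 0.5 (d = cb = -0.35).

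**Single-mediator models (product of coefficients over total effect).**

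- Process measure M alone: a(cb + d)/[a(cb + d)] = 1. The true 100% is recovered in both cases.
- Brief scale P alone: share = r·[f + (1 - f)·q]. With f = 1 this equals r. With f = 0.5 it equals r × (0.5 + 0.5 × 0.20) = 0.6r.
- If the effect reaches S by a route that does not involve M at all, P's share is again r. So the matched result is the same whether M is the whole mechanism or none of it.

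**Combined model, M and P in parallel.** Given T and M, only e and measurement error are left in P. The coefficient of P is therefore c·λ, with

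λ = (1 - q)·r / (1 - q·r).

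The shares are f·λ for the brief scale and 1 - f·λ for the mechanism. Example at r = 0.6: λ = 0.48/0.88 = 0.545. The mechanism's share is then 1 - 0.545 = 0.45 for f = 1, and 1 - 0.273 = 0.73 for f = 0.5.

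| r | λ | M's combined share, f = 1 | M's combined share, f = 0.5 | P alone, f = 1 | P alone, f = 0.5 |
|---|---|---|---|---|---|
| 1.0 | 1.00 | 0.00 | 0.50 | 1.00 | 0.60 |
| 0.9 | 0.88 | 0.12 | 0.56 | 0.90 | 0.54 |
| 0.8 | 0.76 | 0.24 | 0.62 | 0.80 | 0.48 |
| 0.7 | 0.65 | 0.35 | 0.67 | 0.70 | 0.42 |
| 0.6 | 0.55 | 0.45 | 0.73 | 0.60 | 0.36 |

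A simulation with 2,000,000 records per row agreed with these values to within about 0.01.

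**Sensitivity to q.** With a stronger link from mechanism to symptom (q = 0.36) and f = 1, the combined share of M is 0.00, 0.15, 0.28, 0.40 and 0.51 for r = 1.0, 0.9, 0.8, 0.7 and 0.6. The direction is the same and the loss slightly smaller.

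**The case against.** The strongest reply has four parts.

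1. **The joint model is not fixed as parallel.** The article allows structural equation modelling or parametric regression, and weekly data would let a process measure precede a symptom in a serial path. Ordering may be left to an analysis plan that is not shown. This stands as a limit: the absorption result applies to parallel entry. It does not remove the point, because the article itself names both scales as mediators, calls for each mediator's effect in a model holding all of them, and exempts neither. The matched single-mediator models are affected whatever the ordering.

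2. **The size depends on assumed paths.** This stands. If half of the mechanism's effect bypasses week-8 symptoms, it keeps 50-73% rather than 0-45%. The 0% end needs a two-item scale without measurement error.

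3. **The process measures are also modelled one at a time.** This stands. Those models are not distorted in this way, and comparing them with the combined model could reveal the absorption. A reader might infer that the plan hides the real mechanisms altogether; it does not.

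4. **The analysis is exploratory and secondary.** This stands and limits the weight of the point. It does not make the matched-pair estimates informative.

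Two wider readings are tempting and not supported. A reader might extend the point to the two brooding items as mediators of the full brooding scale, but the stated aim of the mediation analyses is the primary outcomes, and brooding is a secondary outcome. A reader might also condemn the cross-domain paths (PHQ-2 to GAD-7, GAD-2 to PHQ-9). The domains are related, but neither scale is a short form of the other domain's outcome, so those paths are not circular.

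The planned instrumental variables do not answer the point. They address unobserved confounding of mediators, not overlap between mediator and outcome.

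**Conclusion.** The point holds for the two matched pairs. As written, the plan treats an early short-form reading of each primary outcome as a candidate mechanism for that outcome.

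- **Matched single-mediator models:** mediation appears whatever the mechanism, provided that the effect arises within 8 weeks and persists to 3 months. In the illustration the apparent share equals the scale's reliability when the whole effect runs through week-8 symptoms, and 0.6 times the reliability when half does.
- **Combined model with parallel entry:** a mechanism that truly carries 100% shows 0-45% if it acts only through week-8 symptoms, and 50-73% if half of its effect bypasses them, for reliability from 1.0 down to 0.6.

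These ranges rest on a linear model and assumed path values. They show direction and possible size and do not predict this trial's result. The primary efficacy comparison, the treatment-rule analysis and the sample size are untouched.

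**What to change.** In the mediation paragraph of the Statistical analysis plan section, and in the full analysis plan:

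- For each primary outcome, leave its matched short form out of the mediator set and out of the combined model: PHQ-2 for PHQ-9, GAD-2 for GAD-7.
- Report PHQ-2 and GAD-2 as weekly symptom trajectories by arm, or use them in mediation models only as earlier symptom levels that precede the mediator, to protect temporal order.
- If PHQ-2 to GAD-7 and GAD-2 to PHQ-9 are of interest, keep them as separate exploratory models.

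In Secondary outcomes, describe the two scales as weekly symptom measures rather than listing them with the process mediators.

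The cost is wording. Data collection does not change and no data are lost; each primary outcome has one variable fewer tested as its mediator.
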